##### Data collection

After pretesting, each participant will complete the validated system usability scale (SUS) [22] providing information on software usability, practicability, and user-friendliness. Additionally, information regarding software aspects that need to be improved will be provided using free text items.

##### Data analysis

The usability of the prototype will be analyzed by determining the SUS score. The score can assume values between 0 and 40. To interpret the result in percent, each score will be multiplied by the factor 2.5 [22, 23]. Single item scores and the average overall score will be calculated. According to the literature, an overall SUS score ≥70 % denotes good usability, while a score ≤50 % indicates a considerable need for improvement [23]. Pretesting will be judged as successful when a SUS score of ≥70 % is reached. The free text items will be structured in NVivo qualitative data analysis software, Version 10 (QSR International Pty Ltd., 2012). The items will be analyzed using a coding scheme which will be developed and refined over time by identifying categories directly from the free text answers. Simple frequencies will be calculated for these categories. All statistical analyses will be performed using IBM SPSS Statistics for Windows, Version 22.0 (Armonk, New York: IBM Corp.).

##### Software modification

If the SUS score and/or the free text items indicate the need to improve the prototype, a set of criteria for software revision will be defined based on these results. The prototype will be modified accordingly. Afterwards, researchers from our institute will check whether all modifications listed in the set of criteria have been adequately implemented and will finally approve the prototype. If not, the procedure of adapting the software and checking the modifications will be repeated until all criteria defined have been adequately addressed.

A written user manual illustrating the usage and functions of eCare*Seniors© will be created.

#### Step 3: integration of the software into the setting

##### Practice and patient recruitment

The feasibility study will be performed to test the newly developed prototype of eCare*Seniors© in real-life primary care. Five practices of our teaching and research practice network (two single practices and three group practices) which did not participate in study steps 1 and/or 2 will be included in this third step of the study. These practices will be randomly chosen from all primary care academic teaching practices of our network. The practices will be asked for study participation by phone. The practice owner and one responsible practice assistant will participate in the study. The software prototype will be installed during an on-site visit of a research team member. The physicians and the practice assistants will be trained on how to use the software and will receive the written user manual. Subsequently, they will consecutively set up eCare*Seniors© for one scheduled patient per day, until it is implemented for 30 patients of the practice. This number is based on the recommendation for sample sizes in pilot studies by Browne [24]. Because the feasibility study is not conducted to estimate effect sizes on practice and/or patient outcomes but to test for the software’s usability in routine primary care, no sample size was calculated.

##### Inclusion and exclusion criteria for patients

The practices will be asked to use eCare*Seniors© for 30 patients aged ≥65 years with more than one chronic disease (multimorbidity) who are taking at least five different chronic medications (polypharmacy).

According to the European General Practice Research Network (EGPRN), multimorbidity is defined as any combination of chronic disease with at least one other acute or chronic disease, or associated or non-associated bio-psychosocial factor, or somatic risk factor (e.g., smoking behavior, chronic job stress, diabetes, heart failure) [2]. We adapted this definition because eCare*Seniors© will be designed to support chronic care management: all seniors with two or more chronic diseases will be eligible for the study.

##### Outcome measures and data collection

The primary outcome of the feasibility study is the usability of eCare*Seniors© which will be measured with the SUS [22] after 3 months of using eCare*Seniors©. The secondary outcomes at 3-month follow-up are the following:Willingness to routinely use the software,Degree of utilization of eCare*Seniors©,Acceptance of eCare*Seniors©,Willingness of primary care physicians to purchase eCare*Seniors©Willingness of practice assistants to use eCare*Seniors© in the long term.

Data will be collected at baseline and after 3 months. At baseline, the data collection will be conducted by a research team member of our institute during the first on-site visit, before installing and explaining the software. All participating physicians and practice assistants will be surveyed using two approaches:Semi-structured interview (in person) about the practice-specific health care management of multimorbid seniors and how their current practice administration system is supporting these processes. The interviews will be audio-recorded and provide information about practice-related specifics of managing multimorbid seniors.Written questionnaire about socio-demographic characteristics and the participant’s computer literacy (validated computer literacy scale (CLS) [25]). These data will be used to characterize the study participants.

After 3 months, a second on-site visit will be conducted for follow-up data collection consisting of three elements. Again, all participating physicians and practice assistants will be surveyed:Semi-structured interview (in person) about the utilization of eCare*Seniors© in the practice. The interviews will be audio-recorded and provide details about the software’s acceptance, the satisfaction with the software, perceived barriers, ideas for improvement, its planned further utilization (practice assistants’ perspective), and the willingness to purchase the software (physicians’ perspective).Validated SUS [22] about the experienced usability of the new software for the primary outcome measurement.Retrieval of the usage data of eCare*Seniors© in each practice, which will be used to determine the frequency and continuity of using the software during the previous 3 months.

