**Fig. 3 Fig3:**
[figure not shown]
Example of the patient-centered visualization strategy of eCare*Seniors© with information flags (chronic diseases, medication) and dynamic action flags (upcoming preventive and therapeutic measures)

The information source for the flags is each patient’s EHR: copied information will be exported and then newly edited using this flag system. The software will not evaluate or interpret any patient data by itself. All flags, including priorities and triggers for dynamic flags, will be selected by physicians themselves, either on an individual (one patient) or group (multiple patients) level. Depending on the rights assigned by the administrator, practice assistants will be entitled to apply dynamic flags for individual care processes in the patient management center, e.g., check-up or immunization intervals. When opening a patient’s EHR, the user interface of the software will automatically pop up in a separate window and provide the physician-selected flags for this individual patient’s health care management.

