##### Data analysis

The primary outcome of the feasibility study, defined as usability of eCare*Seniors©, will be analyzed by determining the SUS score as described in the outline of step 2. The feasibility study will be judged as successful if a SUS score ≥70 % is reached, denoting good usability [23].

The secondary outcome parameters willingness to purchase the software, willingness for continued use of the software, and utilization usage of the software will be determined by calculating the frequencies. These data will be used to offer insights into the attitudes of users regarding the utilization of eCare*Seniors© for everyday patient management.

Audio-recorded data of the interviews will be transcribed. Structuring and coding of the qualitative interview data will be performed in NVivo qualitative data analysis software, Version 10 (QSR International Pty Ltd., 2012). The coding scheme will be developed and refined over time by identifying categories directly from the transcripts. The transcripts will be analyzed by two researchers. Experiences, attitudes, and/or attributes described in the first and in the second interview will be compared to offer insights into reported advantages and disadvantages of eCare*Seniors© compared to the current practice-specific health care management.

All statistical analyses will be performed using IBM SPSS Statistics for Windows, Version 22.0 (Armonk, New York: IBM Corp.).

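### The utilization outcome pools study-scheduled set-up with voluntary use; reporting the period after set-up separately would be a cheap improvement

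*Protocol article*

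**What the plan says.** All of the following is in the protocol article.

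- **Outcome.** *Outcome measures and data collection* (Step 3) lists "Degree of utilization of eCare*Seniors" among the secondary outcomes at 3 months.
- **Source and window.** At the second on-site visit, usage data are retrieved in each practice. They "will be used to determine the frequency and continuity of using the software during the previous 3 months".
- **Analysis.** *Data analysis* (Step 3) states that "utilization usage of the software will be determined by calculating the frequencies".
- **Interpretation.** The same paragraph, which also covers willingness to purchase and to continue, adds: "These data will be used to offer insights into the attitudes of users regarding the utilization of eCare*Seniors© for everyday patient management".
- **Set-up schedule.** *Practice and patient recruitment* (Step 3) states that, after installation and training, "they will consecutively set up eCare*Seniors© for one scheduled patient per day, until it is implemented for 30 patients of the practice".
- **Automatic display.** *Description of the user interface* (text after Figure 3) states that when a patient's electronic record is opened, "the user interface of the software will automatically pop up in a separate window".

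The article does not separate the set-up phase from the time after it. It does not state which logged event counts as use.

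**The concern.** The stated window and the stated interpretation do not match. Entering a patient because the study schedules one entry per day is study procedure. It says little about whether the practice would choose the software for everyday care. The 3 months begin at about the installation visit, so they include the whole set-up phase, and a frequency over the full window adds the two kinds of activity together.

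Continuity is affected as well, because daily set-up would produce an unbroken run of active days at the start of the window.

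The automatic window is a second possible source of mixing. If its display were logged as use, the count would partly measure how often records are opened. Whether it would be logged that way cannot be told from the article.

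The follow-up visit collects interviews, the SUS and usage data. Only the usage data record behaviour; the other two are self-report by one practice owner and one assistant in each of five practices. The log is therefore the one direct check on stated willingness to use the software, and it should be interpretable.

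**Working it through.** The article gives no utilization figure or target, so there is nothing to reproduce. The check is how much of the window the scheduled set-up occupies.

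**Inputs from the article:** one set-up per day; 30 patients of the practice (*Practice and patient recruitment*); a 3-month window (*Outcome measures and data collection*); five practices and 30 seniors (*Abstract*).

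**Assumed, not in the article:** 4 to 5 practice days per week; 12 to 13 weeks in 3 months; no set-up day missed.

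**1. Share of working days taken by set-up** = 30 / (days per week × weeks)

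| Days per week | 12 weeks | 13 weeks |
|---|---|---|
| 5 | 30/60 = 50% | 30/65 = 46% |
| 4 | 30/48 = 63% | 30/52 = 58% |

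At 5 days a week, set-up lasts 30/5 = 6 weeks and leaves 30 to 35 working days. At 4 days a week it lasts 7.5 weeks and leaves 18 to 22.

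**2. If 30 is the total over five practices:** 30/5 = 6 per practice. The share is 6/65 = 9%, and at most 6/48 = 13%.

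**3. Effect on a pooled share of active days.** Let p be the proportion of post-set-up days with voluntary use, and count every set-up day as active. With 65 days:

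- 30 per practice: pooled share = (30 + 35p)/65. For p = 0 this is 46%, for p = 0.25 it is 38.75/65 = 60%, and for p = 0.5 it is 47.5/65 = 73%.
- 6 per practice: pooled share = (6 + 59p)/65. For p = 0 this is 9%, for p = 0.25 it is 20.75/65 = 32%, and for p = 0.5 it is 35.5/65 = 55%.

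On the first reading, the pooled figure is well above the voluntary rate p. On the second, the gap is small.

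**4. Share of events instead of days.** Assume 62 working days, set-ups on days 1 to 30, and v later record openings per patient per quarter, spread evenly. Expected later openings are v × Σ(62 − d)/62 for d = 1 to 30, which is v × 1395/62 = 22.5v. The set-up share is 30/(30 + 22.5v): 57% for v = 1, 40% for v = 2, 25% for v = 4 and 12% for v = 10. The visit rates are assumed. Each of these later openings would also trigger the automatic window.

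The contribution of automatic displays cannot be quantified, because the article does not say which event is counted.

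**The case against.** The strongest points on the other side are these.

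- **The counted event is not fixed.** A condensed article may leave that to the full protocol or analysis plan, and nothing says that an automatic display counts as use. This stands: inflation by the pop-up is a possibility only. The overlap with set-up does not depend on it.
- **Use is not strictly imposed.** *Ethical considerations* leaves the extent of implementation to the physicians, and adherence to the daily schedule is itself feasibility information. This stands in part. The schedule is still a study instruction, and the time after it is where free choice shows best.
- **Interviews also cover utilization and acceptance.** True, but self-report cannot correct a pooled log count.
- **Nothing hangs on the outcome.** Success is a SUS score of at least 70%, and refinement is triggered by the SUS and the interview content. This stands and limits the weight of the point.

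A reader might also infer three stronger conclusions that the documents do not support:

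1. *The measure is largely a product of the protocol.* The base-case share is 46% of days, the share of events may be far lower, and it is 9% of days on the other reading of the 30 patients.
2. *Utilization will look high even if nobody uses the software voluntarily.* About half the window follows set-up at 5 days a week, so a continuity measure could show use falling away, unless displays are counted, which is not stated.
3. *Follow-up is shorter than stated.* The 3 months belong to the physicians and assistants as users. The article does not promise 3 months per patient or after the 30th set-up.

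**Conclusion.** The point holds as a modest, low-cost improvement. As described, the utilization outcome combines scheduled set-up with voluntary use over one 3-month window, while the result is read as users' attitudes to everyday use.

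If 30 patients are set up per practice, set-up fills about 46% of working days at 5 days a week over 13 weeks, and up to 63% at 4 days a week over 12 weeks. If 30 is the total over five practices, it fills 9 to 13%. The Step 3 recruitment text favours the per-practice reading, while the abstract permits the other. All shares assume that no scheduled day is missed. Automatic displays may add to the mixing, but this is not established.

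The consequence is confined to how one descriptive secondary outcome is interpreted. The primary outcome and the success criterion are untouched.

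**What to change.** 1. Report utilization separately for the set-up phase and for the period after each practice's last set-up. Interpret only the later period as routine use.
2. Count user-initiated actions (a flag created, edited, acted on or closed) and leave automatic displays out of the count.
3. Put these log events in the Step 2 software specification. The prototype is still to be built, and events that are not logged cannot be recovered later.

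**Cost:** a small logging requirement, one more line of descriptive analysis, a shorter window for the routine-use figure (about 30 to 35 working days at 5 days a week if 30 patients are set up per practice), and probably a lower reported utilization.

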##### Data analysis

The primary outcome of the feasibility study, defined as usability of eCare*Seniors©, will be analyzed by determining the SUS score as described in the outline of step 2. The feasibility study will be judged as successful if a SUS score ≥70 % is reached, denoting good usability [23].

The secondary outcome parameters willingness to purchase the software, willingness for continued use of the software, and utilization usage of the software will be determined by calculating the frequencies. These data will be used to offer insights into the attitudes of users regarding the utilization of eCare*Seniors© for everyday patient management.

Audio-recorded data of the interviews will be transcribed. Structuring and coding of the qualitative interview data will be performed in NVivo qualitative data analysis software, Version 10 (QSR International Pty Ltd., 2012). The coding scheme will be developed and refined over time by identifying categories directly from the transcripts. The transcripts will be analyzed by two researchers. Experiences, attitudes, and/or attributes described in the first and in the second interview will be compared to offer insights into reported advantages and disadvantages of eCare*Seniors© compared to the current practice-specific health care management.

All statistical analyses will be performed using IBM SPSS Statistics for Windows, Version 22.0 (Armonk, New York: IBM Corp.).

##### Software refinement

If the SUS score and/or the content analyses of the interviews indicate the need to improve eCare*Seniors©, these results will be summarized in a set of criteria which will provide the basis for revision. The revised software prototype will be tested in the practices that participated in the feasibility study. Each participant will test the refined prototype for ten patients of the practice as well as complete the SUS and additional free text items regarding improvements and deteriorations compared to the previous version of the prototype. The SUS and the free text items will be analyzed as described previously to check whether the revised prototype fulfills all aspects according to the predefined set of criteria. If not, this procedure will be repeated until all criteria are met.

### Quality controls and data management

Quality controls will be conducted during all steps of the study. After recruitment, consent forms of all study participants will be checked for completeness. After each data collection, quality controls will be conducted to ensure that required data collection documents are complete. An identification number and the date of birth will be used to verify that study data of each study participant are merged correctly.

Audio-recorded data of the interviews and the focus group sessions will be transcribed. Transcripts will be imported into NVivo qualitative data analysis software, Version 10 (QSR International Pty Ltd., 2012). Quantitative data will be entered manually in an access-restricted electronic database. To control for input errors, 10 % of data will be entered twice. An error rate of 5 % will be accepted; otherwise, all values will be entered twice. The data will be checked for plausibility using simple frequency testing.

All data will be stored access-restricted at our institute.

### Ethical considerations

The study conduct complies with the ethical principles of the World Medical Association Declaration of Helsinki [26]. Ethical approval was obtained from the Ethics Commission of the Medical Faculty of the University of Duisburg-Essen (reference number: 14-5980-BO, date of approval: 01/06/2015). All participating primary care physicians and practices will sign an informed consent form which will be stored at our institute. Throughout the feasibility study, physicians will be free regarding the extent to which they implement eCare*Seniors© in patient care. The responsibility for the patients’ care and health care planning remains solely in the hands of the physician in charge.

## Discussion

This study aims at designing a user-friendly, easy-to-comprehend, workflow-oriented, and comprehensive EHR-based CDSS for primary care physicians and non-medical professions which provides assistance in managing multimorbid seniors. Assuring evidence-based and individual health care for seniors is a key future challenge for physicians given the decreasing resources in the health care sector, the aging population with increasing multimorbidity, evolving diagnostic and therapeutic options, the trend towards an information society with patients who are involved in medical decision-making, and the subsequent diversity of patients’ preferences. Consequently, a well-designed electronic decision support system—such as the one we aim for with eCare*Seniors©—will be relevant to ensure seniors’ comprehensive long-term care.

eCare*Seniors© addresses a health care management problem in a target group of increasing importance in many societies. Potential barriers of CDSS acceptance identified in prior studies [9–11] will be addressed using a bottom-up approach focusing on the end user and the target setting:Aiming at a user-friendly and easy-to-comprehend software solution, end users will be continuously involved in all steps of the software design: the needs of primary care physicians and practice assistants to manage multimorbid seniors will be assessed using focus groups and process observations, the software will be tested in real-life primary care, and repetitive practice tests will be conducted until the software is fully adapted to primary care needs.The continuous involvement of the end users’ perspectives will also contribute to optimal workflow integration of eCare*Seniors©: organizational needs can be identified promptly and taken into account for software design. To prevent additional workload, eCare*Seniors© will allow for setting-specific tailoring of the software: physicians will select which components and functions they want to use for their patient population as well as individual patients. The physician control center as an integral element of the software will support physician managers in improving their settings’ health care for seniors over time.With the objective of maintaining the physician’s autonomy, eCare*Seniors© will provide passive decision support only: the software will offer options but will not replace the physician’s decision-making. The physician control center helps the user to preselect practice-relevant components with relevant information and action flags. Based on this preselection, the software will only suggest options if desired by the physician.To address concerns about negative effects on the physician-patient relationship, eCare*Seniors© will allow for a patient-centered and physician-selected use of the software according to physician and patient priorities: all patient-related flags will be selected by physicians so that patients’ preferences as well as physicians’ priorities can be integrated in the care for each individual patient.For optimal integration into organizational structures and workflows, eCare*Seniors© is designed as a platform with access for physicians and non-medical professionals. According to studies which show that practice assistants are a valuable resource in reducing primary care physicians’ workload, increasing efficiency, and improving chronic care patient management [27, 28], eCare*Seniors© will be designed as a comprehensive, interdisciplinary communication platform allowing for the short- and long-term management of individual patients as well as larger patient groups. This includes the integration of recall options for relevant care processes. In each practice, one physician will serve as an administrator and manage access and editing rights depending on each person’s profession and role within the practice.A comprehensive evaluation of the software based on the latest frameworks available for the evaluation of health information technology will be conducted [14, 29].

After the final approval of eCare*Seniors©, we will aim to demonstrate the software’s effectiveness on seniors’ outcomes in a cluster randomized trial with a larger group of primary care practices.

